### Sample Size

This study is mainly powered on the primary outcome, the detection of a significant difference between the three degrees of care (usual, additional website, additional counseling) on medication adherence as determined by refill records of computerized pharmacy systems. Based on previous research in our population and data from the literature [26], we estimate that the adherence at the start of the study will be 65% in each group with a standard deviation (SD) of 30%. We hypothesize that the intervention given in group II and the intervention given in group III will result in an increase of 10% in adherence to treatment, resulting in mean adherence rates of 75% and 85% in groups II and III, respectively. To detect these differences in medication adherence the estimated group size with a power of 80% and an alpha of .05 (2‐sided) would be 200 in each group, resulting in 600 participants in total.

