### Statistical Methods

The data will be analyzed based on the intention‐to‐treat principle and evaluated using SPSS, with descriptive statistics (mean, median, SD, and interquartile range) being determined for all variables. The data will be presented in quantitative format (eg, biometrics, laboratory results, blood pressure, lifestyle scores, adherence score on the basis of refill data, and the MMS) and in descriptions of observed effects (eg, change in BMQ, determinants for adherence, evaluation of the use of iVAZ, and appreciation of nurse intervention).

To evaluate the difference between the groups, an analysis of variance test will be performed on the outcome measures for the three patient groups. The independent variable will be the three intervention groups. The dependent variable is medication adherence measured with the dedicated calculation of refill data. Specifically, we will compare the difference between the first and last time-point between groups for the primary and secondary outcomes measures. For the intervention groups II and III, we will also compare the outcomes of the clinical data at 16 and 28 weeks. To correct for multiple comparison, a Duncan’s multiple range test will be performed. Furthermore, we will perform a receiver operating characteristic (ROC) curve analysis to compare the outcome of the screening instruments (MMS and BMQ) with the pharmacy refill dates. In the ROC curve plot, specificity of the questionnaire is on the x-axis and sensitivity of the question is on the y-axis.

Plausible relations between parameters of cardiovascular risk factors, motivation to change, socioeconomic class, and parameters of adherence (calculated refill score and BMQ and MMS scores) will be tested in a univariate manner. Individual parameters will be tested for normality using the Kolomogorov-Smirnov test in order to select adequate univariate tests. Multiple logistic regression analysis will be performed to assess the relative importance of selected parameters for the likelihood of low adherence, as defined by the refill data algorithm. In all analyses, potential confounders will be included if they independently changed the beta coefficient for dedicated calculation of refill data by at least 5% or when consensus about inclusion existed within the team of researchers supported by clinical evidence from literature.

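### Duncan's test, named as the multiplicity correction with no stated F-test condition, has a family-wise error of 9.75% when all three arms are equal, not .05

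*Protocol article*

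**What the plan says.** The Statistical Methods section of the protocol article says that "an analysis of variance test will be performed on the outcome measures for the three patient groups", with refill-based adherence as the dependent variable and the change from first to last time-point as the quantity compared, for primary and secondary outcomes alike. It then adds: "To correct for multiple comparison, a Duncan’s multiple range test will be performed".

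The section does not make the Duncan step depend on a significant F test, sets no smaller alpha for it, and names no other way of controlling error across the group comparisons.

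The only significance level stated for the group comparisons is in the Sample Size section: "To detect these differences in medication adherence the estimated group size with a power of 80% and an alpha of .05", given there as two-sided. That section expects separate gains in each intervention arm, "resulting in mean adherence rates of 75% and 85% in groups II and III, respectively", and the group size "would be 200 in each group, resulting in 600 participants in total".

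**The concern.** A sentence that promises a correction for multiple comparisons leads the reader to expect that the chance of any false pairwise claim stays at the stated level. Duncan's test is not built to do that. Its level rises with the number of means spanned, by design.

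The pairwise contrasts carry the trial's conclusions. The Intervention section asks whether the website alone can match website plus consultations, and the sample size rests on distinct gains in groups II and III. If neither intervention changes adherence, an ungated Duncan test declares at least one difference almost twice as often as .05 would suggest. The Introduction itself describes current adherence methods as having limited effectiveness, so this null case is not remote. Because the protocol fixes a named method, this is not a detail left open for a later document.

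**Working it through.** **Inputs.** Three groups and Duncan's test (Statistical Methods); alpha .05 two-sided, SD 30, 10-point steps, 200 per group (Sample Size). Error degrees of freedom: 3 × 200 − 3 = 597. The error rates below do not depend on the SD or on the effect sizes assumed; the power figures do.

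**1. The plan's own figure.** For one 10-point step with SD 30, two-sided .05 and 80% power, n = 2 × (1.960 + 0.842)² × 30² / 10² = 141.3, so 142 per group. The stated 200 is larger and gives 91.5% power for such a step. That the 200 is not reproduced is a separate matter. It matters here only because it leaves room for proper error control.

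**2. Duncan's level.** For a range of p means the level is 1 − (1 − α)^(p−1).
- p = 2: 1 − 0.95 = 5%.
- p = 3: 1 − 0.95² = 9.75%, which is 1.95 times .05.

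**3. Critical values** (studentized range, 597 df).
- Duncan, three means: 2.924; divided by √2, t = 2.068.
- Duncan, two means: 2.777; divided by √2, t = 1.964.
- A true 5% test of the three-mean range (Tukey): 3.323.

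The probability that the range of three equal means exceeds 2.924 is 0.0975.

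**4. Error rates by simulation** (200 per group, SD 30, 1,000,000 trials per setting).

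| True means | Duncan, no gate | Duncan after significant F | Tukey |
|---|---|---|---|
| All three equal | 9.75% | 5.0% | 5.0% |
| II = III, I differs (65/75/75) | 5.0% | 5.0% | 1.9% |
| I = II, III differs (65/65/75) | 5.0% | 5.0% | 1.9% |

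When only two means are equal, just one pair can yield a false claim, and that pair must pass at least the two-mean criterion of 5%.

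**5. Why the gate is enough with three arms.** Write r for the observed range divided by the standard error of a mean. The F statistic is the variance of the three standardised means, which is at most r²/3 (reached when the middle mean coincides with an extreme one). The 5% critical value of F on 2 and 597 df is 3.011. A significant F therefore forces r² > 3 × 3.011 = 9.03, so r > 3.005, which exceeds 2.924. Every significant F already passes Duncan's first step, and the adjacent pairs are then tested at t = 1.964, as in ordinary pairwise tests at .05. Gated Duncan and gated pairwise tests thus make the same decisions; in the simulations they never differed.

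**6. Power cost of the gate** (SD 30, 200 per group).

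| Means I/II/III | Contrast | Duncan, no gate | Gated | Tukey |
|---|---|---|---|---|
| 65/75/85 | I vs II | 91% | 91% | 84% |
| 65/70/75 | I vs III | 90% | 85% | 84% |
| 65/65/75 | I vs III | 91% | 90% | 84% |
| 65/70/70 | I vs III | 36% | 30% | 25% |

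Under 65/75/85 the overall F test has power above 99.9%, so the gate almost never closes.

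**The case against.** The strongest reply is that the text describes an analysis of variance first and Duncan's test second, and that the sample size is framed around a difference among the three degrees of care, which is the overall question. Read as a sequence, Duncan's test would follow only a significant F, and the family-wise error would be 5%. That reading is natural, and on it the excess disappears. But the text does not state it, a multiple range test can be run without a significant F, and the choice moves the error between 5% and 9.75%. A condition that matters this much should be written down.

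A second reply is that the .05 belongs to the sample size statement, and that the document nowhere claims in so many words to hold the family-wise error at .05. This is true. Yet no other level is given, and the Duncan step is presented as a correction.

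Some stronger readings are tempting and should be set aside:
- A reader might infer a 9.75% false-positive risk whatever the truth. It applies only when all three means are equal and no gate is used.
- A reader might infer that Duncan's test has to go. Step 5 shows that the stated gate is sufficient.
- A reader might infer that error control is free. That holds near 65/75/85 but not for smaller effects.
- A reader might fault the plan for lacking confidence intervals. Nothing in the text excludes them, and an article may leave such reporting detail to the full protocol or analysis plan.

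**Conclusion.** The point stands, with limits. As written, the named correction does not hold the two-sided .05: with three arms and no F-test condition, its family-wise error is 9.75% when all three means are equal and about 5% when only two are. The overall F test itself keeps 5%, and no endpoint, sample size or data collection is affected, so severity is moderate.

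The error rates assume normal errors with equal variance and equal group sizes, and cover the three comparisons on one outcome only, not the set of secondary outcomes. The power figures also assume SD 30, which the protocol gives for adherence at the start of the study. The planned comparison is of change from first to last time-point, whose SD is not stated.

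**What to change.** Add one sentence to Statistical Methods, before unblinded analysis: pairwise comparisons between groups are made only if the overall three-group F test is significant at two-sided .05. With exactly three arms this gives 5% family-wise error whether the pairs are then tested by Duncan's test or each at .05. Alternatively, replace Duncan's test with a procedure that controls the family-wise error by itself, such as Tukey or Holm.

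The cost is the power shown in step 6: essentially none for the gate under 65/75/85, about 5 points for I versus III under 65/70/75, and about 1 point under 65/65/75. Tukey lowers power for a 10-point step from about 91% to about 84%, still above the planned 80%. No change to sample size or data collection is needed.

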#### Group and Individual Consultations (Group III)

For group III, the intervention program will also include a single group consultation of 60 minutes led by a nurse and a pharmacist followed by two individual consultations of 30 minutes with a nurse.

During the group consultations patients receive information about their disease, cardiovascular medication (statins and antihypertensive and antithrombotic agents), and the importance of treatment adherence. Patients will receive an information booklet with all information presented during the plenary session. At the end of this consultation patients are asked to keep a diary of their medication intake during a 2-week period and to set a personal goal for the upcoming individual consultation with a nurse. The group consultation is regarded as an efficient way to increase knowledge and understanding of the risks. It also provides a gathering with other patients (peers).

During individual consultations, the intervention is further tailored based on the goal previously set, patient’s concerns, and necessities using the results of the screening questionnaire (see Data Collection). The following topics will be discussed during the individual consultation: patient's motivation and confidence (barriers, concerns, and positive self-motivational statements about their adherence behavior), options for increasing adherence to treatment, and a global summary of the counseling session.

Both the group and the individual consultations take place at the outpatient clinic. The involved nurses have had training in motivational interviewing [21] and were especially trained for this intervention by a psychologist.

For each of the constructs, we used the recommended behavior change strategies [12,13]. We tailored the intervention further by using the taxonomy of Abraham and Michie [22,23] and the coding manual by de Bruin [24] to categorize the behavior change techniques to be included in the intervention. For each of the components of HBM, the determinants, techniques, and application strategy were developed and are detailed in Figure 1-4.

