### Secondary Outcomes

All secondary outcome measurements will be obtained just before inclusion (in the usual care screenings program) and one year after inclusion. The secondary outcome measurements include clinical responses to drug therapy (eg, cholesterol level), self-report questionnaires, and changes in systolic blood pressure.

Clinical responses to drug therapy will be recorded. A recorded low-density lipoprotein cholesterol level above 20% of preestimated low-density lipoprotein cholesterol reduction during follow-up will be considered as possible indication of poor adherence. If the patient also uses antihypertension drugs, the blood pressure on baseline will be compared to blood pressure after one year and will need to be within target blood pressure for cardiovascular risk management (systolic <135 mm Hg). These office blood pressure measurements are performed according to the recommendations of the European Society of Hypertension [15] with a validated automated device; data will be based on a mean of four office measurements.

Second, two validated self-report questionnaires will be used. The MMS will be used to measure adherence [17]. Each of the 8 items measures a specific medication‐taking behavior. MMS scores can range from 0 to 8 and can be classified into three levels of adherence: low adherence (score of less than 6), medium adherence (score of 6 to less than 8) and high adherence (score of 8) [31]. The BMQ will be used to provide information about the beliefs, perceived necessity, and concerns patients have regarding their illness and prescribed medication [18]. Respondents indicate their degree of agreement with each individual statement about medicines on a 5‐point Likert scale. It is then possible to differentiate between patients on the basis of their beliefs about the necessity of their medication and their concerns about taking it. Patients can be classified into four different categories: accepting (high necessity and low concerns), ambivalent (high necessity and high concerns), skeptical (high concerns and low necessity), and indifferent (low concerns and low necessity) [32,33].

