### Data Collection and Management

The primary data collected will be provided by the initial screening. Obtained data from the screening are blood lipid levels, blood pressure, waist circumference, body mass index, blood glucose levels, and medication use. Lifestyle is evaluated through a questionnaire which is a compilation of existing validated questionnaires regarding demographic data, smoking, alcohol use, physical activity, and eating habits. For each of these lifestyle issues, patient’s motivation to change is evaluated [16]. Adherence is measured by the MMS [17] and beliefs about medication by the BMQ [18].

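### The determinant analyses do not commit to keeping randomised group in the model; if one-year values are used, some associations with adherence could reflect only the arm

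*Protocol article*

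**What the plan says.** The last paragraph of analysis methods in Statistical Methods sets out the determinant analyses. On one side it places cardiovascular risk factors, motivation to change and socioeconomic class; on the other, adherence. The relations "and parameters of adherence (calculated refill score and BMQ and MMS scores) will be tested in a univariate manner". Each parameter is first checked for normality "in order to select adequate univariate tests".

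Then "Multiple logistic regression analysis will be performed to assess the relative importance of selected parameters for the likelihood of low adherence", with low adherence defined from the refill data. A selection rule follows: "In all analyses, potential confounders will be included if they independently changed the beta coefficient for dedicated calculation of refill data by at least 5" per cent, or if the research team agrees on inclusion.

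Randomised group is named as the independent variable for the analysis of variance in the preceding paragraph. It is not mentioned for the determinant analyses, and neither is an analysis within arms or in controls only.

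Two other places bear on the point. Sample Size plans for adherence to differ by arm, from 65% with an SD of 30%, "resulting in mean adherence rates of 75% and 85% in groups II and III, respectively". Secondary Outcomes gives the timing for cholesterol, blood pressure, MMS and BMQ: "All secondary outcome measurements will be obtained just before inclusion (in the usual care screenings program) and one year after inclusion". So values from before and after randomisation will both exist for several of the parameters.

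**The concern.** The natural question for a determinant analysis is whether a parameter and adherence are related among patients treated alike. A univariate test over all three arms asks instead whether they are related in the mixture of arms. The two questions differ when arm moves both variables.

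The protocol expects arm to move refill adherence. The website shows patients their own cholesterol, blood pressure and lifestyle so that they will act on them, so the arm could also move the one-year values of these parameters. Arm is then a common cause. The pooled test can reject because both variables rose or fell with arm, even with no relation within any arm.

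At stake is the list of determinants of adherence, which Statistical Methods names among the results to be described. A parameter could be reported as a determinant when its association only restates which arm the patient was in.

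**Working it through.** The document gives no figure for the determinant analyses, so there is none to reproduce. The check is how far a pooled test departs from its nominal 5%.

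**Inputs from the protocol (Sample Size).** 200 patients per arm, 600 in total; adherence means 65/75/85; SD 30; two-sided alpha .05. The refill step per arm is 10/30 = 0.333 SD.

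**Assumptions.** The parameter shifts by d SD per arm step (I to II to III). The document gives no value for d, so a range is shown. Within each arm the parameter and adherence are unrelated.

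**Formula.** Arm scores 0, 1, 2 in equal numbers have variance 2/3. The pooled correlation is

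r = (2/3 × 0.333 × d) / √[(1 + 2/3 × 0.333²)(1 + 2/3 × d²)]

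and the test statistic is centred near r × √600 = 24.49 r.

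- d = 0.1: r = 0.0222 / √(1.0741 × 1.0067) = 0.021; centre 0.52; rejection about 8%.
- d = 0.2: r = 0.0444 / √(1.0741 × 1.0267) = 0.042; centre 1.04; rejection about 18%.
- d = 0.333: r = 0.0741 / 1.0741 = 0.069; centre 1.69; rejection about 39%.

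**Simulation (6,000 trials per setting).**

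| Shift d per step | Pooled, 65/75/85 | Pooled, 65/75/75 | Arm in model, 65/75/85 |
|---|---|---|---|
| 0 (baseline value) | 4.9% | 5.1% | 4.9% |
| 0.1 | 8.5% | 5.6% | 5.2% |
| 0.2 | 17.7% | 7.6% | 5.3% |
| 0.333 | 39.9% | 14.6% | 4.9% |

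If the intervention does not change adherence, the pooled rate stays at about 5% whatever the shift. A t-test of the parameter between patients below 80% adherence and the rest gives 7%, 14% and 28% at d = 0.1, 0.2 and 0.333 under 65/75/85 (4,000 trials per setting).

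**Baseline parameters.** Randomisation makes them independent of arm, so there is no bias. Leaving arm out keeps its effect on adherence in the error variance, which shrinks a within-arm correlation ρ to ρ/√1.0741. For ρ = 0.10 this is 0.0965, and power falls from about 69% to 66%. Simulated power for ρ = 0.08, 0.10 and 0.115 is 47%, 67% and 77% without arm, against 50%, 70% and 80% with arm.

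**The case against.** The strongest reply is that the protocol never says the arms are pooled or that group is excluded, and that an article may leave the covariates of an exploratory analysis to the full plan. The first part is right: pooling is the plain reading, not a statement. But the article does state a method, and a univariate test cannot contain group.

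Baseline values are also a natural reading. Data Collection and Management says "The primary data collected will be provided by the initial screening" and lists lipids, blood pressure, lifestyle and motivation there. On that reading only the small loss of power remains. The text does not settle it.

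The confounder rule is a real safeguard. In this setup (4,000 trials per setting, linear model, arm offered as a candidate), arm met the 5% criterion in 97% of the pooled false positives at d = 0.1 and in all of them at 0.2 and 0.333. The error rate under the rule was 4.6% to 5.5%. But the rule does not name group and cannot act in the univariate step. It therefore narrows the problem without removing it.

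For lipids and blood pressure, part of any association may be genuine, because better adherence lowers both. Zero relation within arms is a device to isolate the artefact, not a forecast.

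A reader might infer that BMQ or MMS scores would be falsely reported as determinants of adherence. The sentence puts both on the adherence side. Nor can arm move socioeconomic class. A reader might also point to the group III consultations, which discuss "patient's motivation and confidence (barriers, concerns, and positive self-motivational statements about their adherence behavior"). That concerns medication taking, whereas motivation to change in the analysis is asked about lifestyle issues, and Secondary Outcomes does not list it among the one-year measures.

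**Conclusion.** The concern holds in a conditional form. The determinant analyses do not commit to keeping randomised group in the univariate tests or in the logistic regression. Bias arises only if one-year values are used and the intervention moves both the parameter and adherence. Under the protocol's own 65/75/85 the false-positive rate is then about 8% to 40% for assumed shifts of 0.1 to 0.33 SD per arm step. Under 65/75/75 it is about 6% to 15%. The spurious correlations are small, about 0.02 to 0.07 under 65/75/85, or less than 0.5% of variance (0.069² = 0.0048). With baseline values the only cost is about 2 to 4 points of power.

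The documents do not support the stronger reading that false determinants will appear, since that needs conditions the text leaves open. They also give no ground for doubting the randomised comparison of adherence, which this point does not touch. It is a minor improvement to a secondary analysis, worth making because group in the model is better under either reading.

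**What to change.** In Statistical Methods, replace the univariate testing of these relations with a test of each parameter in a model that contains randomised group as a three-level factor. For non-normal parameters, use a rank correlation partialled on group. State that group is always kept in the multiple logistic regression for low adherence, whatever the 5% change-in-beta rule gives. State for each parameter whether the baseline or the one-year value is used.

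The cost is a few sentences of analysis wording and two degrees of freedom among 600 patients. No new data, visits or patients are needed.

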### Assignment of Interventions

Patients who meet the criteria and consent to participate will then be randomized by the nurse stratified by department (eg, neurology, vascular surgery, and cardiology) in a 1:1:1 ratio into one of the three groups using computer randomization.

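### The confounder-selection rule is worded for all analyses, so the randomised comparison can be read either as unadjusted or as adjusted for covariates picked on the observed estimate

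*Protocol article*

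**What the plan says.** Two paragraphs of Statistical Methods bear on this point.

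- **Between-arm comparison.** The plan states that "an analysis of variance test will be performed on the outcome measures for the three patient groups". It adds "The independent variable will be the three intervention groups" and "The dependent variable is medication adherence measured with the dedicated calculation of refill data". The contrast is the difference between the first and last time-point, followed by Duncan's test. No covariate is named.
- **Determinants of adherence.** The next paragraph covers univariate relations and then a regression: "Multiple logistic regression analysis will be performed to assess the relative importance of selected parameters for the likelihood of low adherence". It closes with the covariate rule: "In all analyses, potential confounders will be included if they independently changed the beta coefficient" for the refill calculation "by at least 5% or when consensus about inclusion existed within the team of researchers supported by clinical evidence from literature".

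Under Assignment of Interventions, patients are "randomized by the nurse stratified by department (eg, neurology, vascular surgery, and cardiology) in a 1:1:1 ratio". Department is not mentioned as a covariate anywhere in Statistical Methods.

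**The concern.** A change-in-estimate rule is designed for observational data, where a covariate that moves the exposure coefficient may be a confounder. Under randomisation, a baseline covariate moves the group coefficient only through chance imbalance. A relative threshold then selects on noise in the estimate, and does so most readily when the estimate is near zero, because 5% of a very small number is very small.

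The second route into the model is team agreement backed by literature. It has no date and no fixed list. If the rule governs the primary comparison, the model behind the reported effect and its confidence interval is settled only once the result is visible. If it does not, the words about all analyses are wrong. A reader of this document cannot tell which analysis is primary.

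**Working it through.** No figure in the plan is disputed here, so there is none to reproduce. The check has three steps.

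**1. Scope, from the text.** The ANOVA paragraph gives group as the only independent variable, which points to an unadjusted analysis. The rule's opening words cover every analysis and nothing exempts the ANOVA, which points to a data-adjusted analysis. Two features favour a narrow reading: the rule closes the logistic-regression paragraph, and it speaks of a beta coefficient for the refill calculation, although refill adherence is the dependent variable in the ANOVA. The text does not settle the matter.

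**2. How easily a non-confounder passes 5%.** From Sample Size: 200 per arm, SD 30 points, difference 10 points. Assumed: a standardised baseline covariate correlated 0.15 with the outcome.

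- SD of the chance imbalance between two arms: √(2/200) = 0.10.
- SD of the resulting shift in the estimate: 0.15 × 0.10 × 30 = 0.45 points.
- With a 10-point effect, the threshold is 0.05 × 10 = 0.5 points. P(|Z| ≥ 0.5/0.45) = P(|Z| ≥ 1.11) ≈ 27%.
- With no effect, the estimate itself has SD 0.10 × 30 = 3 points. Treating shift and estimate as independent normals, their ratio is Cauchy with scale 0.45/3 = 0.15. P(|ratio| ≥ 0.05) = 1 − (2/π)·arctan(0.05/0.15) ≈ 80%.

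Simulation with ten such covariates gives 28% (2,000 trials with the effect) and 77% (4,000 trials without), close to these approximations. None of the covariates is a confounder in either case.

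**3. Type I error.** Simulated with no effect, two arms of 200, and 4,000 trials per row. K is the number of balanced baseline covariates and R² the outcome variance they jointly explain; both are assumptions, varied over a range. The Monte Carlo standard error near 5% is √(0.05 × 0.95/4000) ≈ 0.34 percentage points. The last column takes the smallest p-value among the unadjusted, single-covariate, rule-selected and full models.

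| K | R² | Share selected | Unadjusted | Fixed set | 5% rule, mechanical | Most favourable model |
|---|---|---|---|---|---|---|
| 5 | 0.1 | 75% | 5.00% | 5.28% | 4.82% | 7.82% |
| 5 | 0.3 | 87% | 5.30% | 5.20% | 4.05% | 10.32% |
| 5 | 0.5 | 90% | 4.75% | 5.42% | 3.78% | 12.32% |
| 10 | 0.1 | 65% | 5.58% | 5.68% | 5.50% | 8.98% |
| 10 | 0.3 | 80% | 5.28% | 5.32% | 4.28% | 11.32% |
| 10 | 0.5 | 86% | 5.20% | 4.85% | 3.30% | 12.82% |

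The step 2 setting (ten covariates at 0.15) agrees: 4.1% for the mechanical rule, 4.7% for a fixed set, and 9.5% for the most favourable model.

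**The case against.** The strongest reply is that the rule was never meant for the randomised comparison. That comparison has its own paragraph with group as the only factor, and the rule's position and its odd reference to a beta coefficient both suit the determinants regression. This is a plausible account of the intention. It does not remove the point, because the wording goes further than that intention and the remedy is to say what was meant.

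A second reply is that covariate lists are commonly left to an analysis plan. That is true, and the absence of a list is not the complaint. The complaint is a rule that this document does state, with a scope that does not suit a randomised comparison.

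Three stronger readings are tempting, and the documents do not support them.

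- **That the trial's type I error is lost.** Applied mechanically, the rule stays at or below about 5.5% in every setting. Inflation requires picking the most favourable model, which the plan nowhere proposes.
- **That consensus is unconstrained.** It must rest on clinical evidence from the literature. This narrows the route, although it fixes neither a list nor a date.
- **That the treatment effect would be adjusted away through motivation, MMS or BMQ scores.** These appear among parameters for univariate testing, and MMS and BMQ are measured again at one year. No text proposes follow-up values as covariates in the between-arm comparison.

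**Conclusion.** The point stands as a fault in a stated rule. As worded, the rule reaches the randomised comparison and conflicts with the ANOVA description, so the primary analysis has two readings. On the adjusted reading, covariates enter because of chance imbalance. With no effect, 65% to 90% of balanced candidates pass the threshold, and the adjusted estimate therefore depends on the observed data.

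The effect on error rates is limited: about 3% to 6% if the rule is mechanical, and about 8% to 13% only if the undated consensus route is used to choose the most favourable model. These figures rest on assumed numbers and strengths of covariates and on a single two-arm comparison, not on the three-arm ANOVA with Duncan's test. They show direction and rough size and do not predict this trial's error rate. The change should be made, but the point does not by itself put the trial's conclusion in doubt.

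**What to change.** - Replace the opening words of the rule so that the 5% criterion and the consensus criterion apply only to the exploratory logistic model for determinants of low adherence.
- For the between-arm comparisons, fix the covariates in advance: department, as the stratification factor, and the outcome's pre-randomisation value where it can be calculated. Alternatively, state that these comparisons are unadjusted.
- Allow only pre-randomisation covariates, and report any further adjustment as sensitivity analysis.

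This is a change of wording with no effect on conduct. It has two small costs. The team gives up discretion over the model. Some patients, all diagnosed within the last 6 months, may also have too little earlier refill history for a baseline value, so the plan should say how they are handled if that covariate is chosen.
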